**MI and proprioception**
Correlations between MI and proprioception measures (elbow 30°, 60°, and 90°, and shoulder 90° flexion and abduction) will be conducted.Regression models will evaluate predictors of proprioceptive performance, with covariates age, dominance, and residual limb length.
**Amputee-specific analyses**
Dominant-side amputation will be coded as a binary variable (yes or no).Differences in MI, functional outcomes, and proprioception outcomes between participants with amputation of the dominant limb and participants with amputation of the nondominant limb will be analyzed using appropriate parametric or nonparametric tests.Associations with MI outcomes will be examined using correlation and regression analyses.
**Missing data, outliers, and multiple comparisons**
Missing data will undergo listwise deletion.Trials with outlier values exceeding 2 SDs from the group mean will be excluded. Sensitivity analyses with and without outliers will be performed.The Bonferroni correction will be applied for multiple comparisons.

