### JPS Description

To evaluate proprioceptive function relevant to prosthetic control, the JPS assessment will be used. JPS measures an individual’s ability to replicate a given joint angle and can be conducted using combinations of passive and active movements, under eyes-closed conditions [22].

Considering the amputation levels of the individuals who have undergone transradial amputation, all participants will undergo JPS assessment of the shoulder and elbow joints, performed bilaterally (dominant and nondominant sides where applicable) with standardized positioning while standing comfortably with feet shoulder-width apart and arms relaxed at the side before each trial. In the amputee group, assessments will be conducted with the prosthesis worn and the terminal device maintained in the closed position to ensure consistency across participants. For passive JPS, the investigator will move the limb to the target angle (eg, 30°) and then return it to the starting position, and the participant will estimate the joint angle without moving it. Participants’ vision will be occluded during assessment to prevent visual feedback, ensuring blinding to the target angle. For active JPS, the investigator first demonstrates the target angle with the participant’s eyes open. Subsequently, with eyes closed, participants actively replicate the joint angle without any physical guidance.

For the shoulder joint, angles of 90° abduction and 90° flexion will be used; and for the elbow joint, angles of 30°, 60°, and 90° flexion will be assessed. All joints will be positioned consistently at the same starting reference point for each trial to ensure measurement consistency across participants. Each angle will be measured 3 times, and the mean value will be recorded. Trials with outlier values exceeding 2 SDs from the mean or trials with measurement errors will be excluded.

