**Significance**
All tests will be 2-tailed, with *P*<.05 considered statistically significant.

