## Results

This study was approved by the noninterventional clinical research ethics committee of Istanbul Medipol University (E-10840098-202.3.02-2988) on May 9, 2024. Following funding from the TÜBİTAK on April 25, 2025, participant enrollment began. As of November 2025, a total of 16 participants have been recruited, including 8 (50%) individuals with transradial amputation and 8 (50%) healthy controls. All assessments for these participants have been completed, and the data have been entered into the study database. Preliminary data cleaning has started; however, statistical analyses have not yet been conducted. Recruitment and data analysis are ongoing, with study completion expected by June 2026.

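### The 2-SD outlier rule is stated against two different means; on one reading it can never act, and on the other it removes valid readings from the main analysis

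*Protocol article*

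**What the plan says.** The rule appears in two places in the protocol article.

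- **JPS Description (Methods):** "Each angle will be measured 3 times, and the mean value will be recorded". The next sentence reads "Trials with outlier values exceeding 2 SDs from the mean or trials with measurement errors will be excluded". It does not say which mean. Measurement error is listed as a separate ground, so the 2-SD ground also covers readings with no known fault.
- **Textbox 2, Missing data, outliers, and multiple comparisons:** "Trials with outlier values exceeding 2 SDs from the group mean will be excluded", followed by "Sensitivity analyses with and without outliers will be performed". The same entry says "Missing data will undergo listwise deletion".

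Textbox 2 defines group 1 as amputees and group 2 as controls, with 15 planned in each. It sets a two-tailed .05 level. Imagery variables are compared between groups by analysis of covariance, with nonparametric methods as the fallback. JPS enters correlations and regressions with imagery, and a comparison of dominant-side with nondominant-side amputation within the amputee group.

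On timing, the Results section says of the 16 participants assessed so far: "Preliminary data cleaning has started; however, statistical analyses have not yet been conducted".

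**The concern.** The two statements name different reference means and are never reconciled, so two analysts could follow the plan and delete different readings.

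Neither reading does what an outlier rule should do. Measured against its own three readings, a trial cannot qualify. Measured against the group, a trial qualifies because the person is unlike the others, which is not evidence of a bad reading.

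Two things are at stake. Deleting the tails within each compared group shrinks the SD used in the test, so P values come out too small. Deleting extreme performers also removes people who carry much of the information on how imagery relates to function and proprioception.

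**Working it through.** **Inputs from the article:** three readings per angle; a 2-SD threshold; 15 per group; a two-tailed .05 level; analysis of covariance for group comparisons of imagery variables.

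**Inputs assumed, because the article gives none:** data shape (normal, t with 5 and 3 df, lognormal, half-normal); intraclass correlation (ICC) of repeated trials from 0 to 0.9; true correlation from 0.3 to 0.7. Every simulation uses data with no faulty readings and one pass of deletion.

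**1. Three readings against their own mean.** The largest possible deviation among n values, in sample SDs, is (n − 1)/√n. For n = 3 this is 2/√3 = 1.155. Readings 0, 0, 3 reach it: mean 1, sum of squares 1 + 1 + 4 = 6, SD = √(6/2) = 1.732, and (3 − 1)/1.732 = 1.155. With divisor n the SD is √(6/3) = 1.414, and the limit is 2/1.414 = 1.414. Both are below 2. In 200,000 simulated triplets the rule fired 0 times. With the sample SD at least six readings are needed (5/√6 = 2.041).

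**2. One score per participant, deletion beyond 2 SDs of the own-group mean, no true difference.** Normal data lose 3.25% of values, about one of the 30 (0.0325 × 30 = 0.98), and 71% of data sets lose at least one.

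| Test | No deletion | After deletion |
|---|---|---|
| t test, normal data (200,000 runs) | 5.0% | 9.45% |
| Analysis of covariance, two covariates (20,000 runs) | 5.0% | 9.3% |
| t test, non-normal shapes | 3.7-4.9% | 8.1-9.8% |
| Rank-sum, all shapes (20,000 runs each) | about 5% | 7.3-8.4% |
| t test, normal data, SD pooled over all 30 | 5.0% | 5.0% |

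The first row reproduces the nominal .05 before deletion.

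**3. Three trials per participant, deletion among the 45 trials of each group, remaining trials averaged (100,000 runs).** About 4% of trials are deleted. Type I error of the group comparison:

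| ICC | 0 | 0.3 | 0.5 | 0.7 | 0.8 | 0.9 |
|---|---|---|---|---|---|---|
| After deletion | 10.2% | 9.4% | 8.7% | 7.9% | 7.9% | 8.1% |

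Without deletion it is 4.9-5.1% throughout.

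**4. Correlations in 15 participants.**

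| Deletion | Correlation | Mean r | Power |
|---|---|---|---|
| JPS trials only, imagery score untouched (ICC 0.5 or 0.8) | 0.5 | 0.49 → 0.47 | 50% → 47% |
| By participant, one variable | 0.5 | 0.49 → 0.45 | 50% → 42% |
| By participant, both variables | 0.3 | 0.29 → 0.24 | 19% → 14% |
| By participant, both variables | 0.5 | 0.49 → 0.42 | 50% → 37% |
| By participant, both variables | 0.7 | 0.69 → 0.62 | 88% → 73% |

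With no true correlation the false-positive rate stays near 5%, so the harm here is attenuation and lost power.

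**5. Comparison inside the amputee group.** With 8 against 7 participants, trimmed at the mean of all 15, type I error is 5.2% against 5.1% untrimmed. There is no material inflation.

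**The case against.** The strongest reply concerns scope. Both statements speak of trials. JPS and the Functional Reach Test have repeated trials, and the Orientate task has repeated images. The MIQ-3, the primary outcome, is a questionnaire averaged over items, and the Box and Block Test is one count. A reader might infer that the primary comparison runs at nearly double its stated error rate. The article does not support that, because it does not say whether the rule reaches single scores. The 9.4% is therefore conditional.

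Nor does Textbox 2 list an amputee-control comparison of JPS, where the rule most plainly applies. The JPS analyses it does list keep close to 5%, and trial-level deletion there costs little correlation. That stands too. The 8-10% applies only where trial-level measures are compared between the two groups after trimming within each.

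The JPS section's unspecified mean could also be read as the group mean that Textbox 2 names. That would remove the contradiction but leave the deletion of valid readings in both places.

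The article also commits to results with and without outliers, so dependence on the exclusions would be visible. This mitigates the problem. It does not cure it, because exclusion is the stated rule and nothing says which result decides if the two differ.

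Two further inferences are not supported. Listwise deletion is stated for missing data, not for excluded outliers, so it does not follow that an outlying trial removes the participant. And the Results section says only that cleaning has begun; it does not say that any value was removed under this rule.

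**Conclusion.** The point holds in conditional form and should be fixed. The 2-SD rule has two unreconciled reference means. Against three readings it cannot operate, which is a matter of algebra and needs no assumption. Against the group mean it removes technically valid readings from the stated main analysis.

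The size depends on how the rule is applied. With trimming inside each group of 15 before an amputee-control comparison, type I error is about 9.4% instead of 5% for single scores (if the rule covers them), about 7-8% with rank tests on single scores, and about 8-10% with trial-level deletion. With the SD pooled over the compared participants there is no inflation. For correlations the loss is small under trial-level JPS deletion (r of about 0.49 to 0.47, power 50% to 47%). It is larger (0.49 to 0.42, power 50% to 37%) only if both variables are trimmed by participant. These figures rest on the assumed distributions, ICCs and true correlations given above, none of which the article supplies.

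**What to change.** State one rule, in the same words, in the JPS section and in Textbox 2:

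- A reading is excluded only for a measurement fault that the assessor documents at the time of testing.
- All technically valid values enter the main analysis, which is named as the deciding one.
- The 2-SD version is kept as a labelled sensitivity analysis. It names its reference mean and the outcomes it covers, and is computed once on the final data.

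Check the cleaning log for the 16 participants already entered. If the 2-SD rule has been applied there, reverse it.

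The cost is a change of wording in two places and one look at the log; no new data are needed. The downside is that genuine extreme values stay in the main analysis, and the sensitivity analysis already planned shows how much they matter.

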**Significance**
All tests will be 2-tailed, with *P*<.05 considered statistically significant.

## Results

This study was approved by the noninterventional clinical research ethics committee of Istanbul Medipol University (E-10840098-202.3.02-2988) on May 9, 2024. Following funding from the TÜBİTAK on April 25, 2025, participant enrollment began. As of November 2025, a total of 16 participants have been recruited, including 8 (50%) individuals with transradial amputation and 8 (50%) healthy controls. All assessments for these participants have been completed, and the data have been entered into the study database. Preliminary data cleaning has started; however, statistical analyses have not yet been conducted. Recruitment and data analysis are ongoing, with study completion expected by June 2026.

## Discussion

### Expected Outcomes

This study protocol is designed to compare MIA between individuals who have undergone transradial amputation and use myoelectric prostheses and healthy individuals as well as evaluate the impact of this ability on upper limb functionality and proprioceptive sensation. By assessing MI capacity, upper extremity function, and proprioception together, this study aims to provide a multidimensional perspective on cognitive and sensorimotor processes in this population.

Existing literature indicates that a high level of MIA may positively influence functional performance and proprioceptive sensation in individuals who have undergone amputation, particularly enhancing functional gains during the preprosthetic and early prosthetic use phases [17,19]. Previous studies involving unilateral upper limb prosthesis users have shown that individuals who have undergone amputation can perform similarly to healthy individuals on hand mental rotation tasks, which are considered cognitive indicators of MIA [42,43]. These findings suggest that the reorganization of body schema following amputation could support MI processes. In line with this, McClanahan et al [44] demonstrated that individuals who have undergone transradial amputations and use myoelectric prostheses can achieve high levels of muscle coordination during prosthesis use, potentially preserving motor control strategies and contributing positively to MIA. With this background, our study is expected to contribute by evaluating the similarities and differences reported in the literature within our own sample, considering body schema reorganization, motor control strategies, and prosthesis use experience.

In previous research, both self-report and performance-based assessment tools, such as the MIQ-3, MCT, and Orientate app, have been shown to be effective in evaluating MIA [45]. For example, Martínez-Rolando et al [46] combined subjective visual and kinesthetic imagery ratings with performance-based measures of response time and accuracy. Similarly, Saruco et al [47] used the MCT to investigate temporal congruence between imagined and actual movement durations in individuals who have undergone lower limb amputation. These approaches demonstrate that MI can be evaluated not only in terms of vividness but also in temporal accuracy. In addition, mobile apps, such as Orientate, integrate imagery tasks with timing measurements, providing an objective assessment of both subjective and temporal parameters [48]. In alignment with this evidence, our study will incorporate these 3 parameters to obtain more comprehensive and objective data regarding the cognitive-motor capacity of individuals who have undergone amputation.

Ensuring that upper extremity function assessments are both reliable and clinically relevant is essential for prosthesis users. The literature identifies the BBT, the JTHFT, and the QuickDASH questionnaire as valid, reliable, and practical tools in clinical settings [49]. Our protocol includes these assessments to objectively measure motor performance and functionality. Furthermore, as shown by Gu et al [50], upper extremity motor skills may be closely related to neural activity during MI, highlighting the cognitive-motor link. Therefore, using a combination of QuickDASH, BBT, and JTHFT is expected to allow a comprehensive evaluation of both subjective and performance-based functional outcomes.

Proprioception, particularly JPS, plays a key role in effective motor control and may also influence MI processes. Clinical and digital JPS assessments, using both active and passive movements, have demonstrated accuracy and reliability [24,40]. In this protocol, proprioception will be evaluated using the DrGoniometer app, chosen for its validated accuracy and ability to perform digital angular measurements [51,52]. Shoulder abduction and flexion and elbow flexion at predefined angles will be assessed to ensure standardization. Previous studies suggest that proprioceptive feedback can enhance prosthetic control and support MI by aligning mentally simulated movement with sensory representations [26,53].

By integrating MI, upper limb function, and proprioception assessments, this study protocol aims to explore their interrelationships in a novel way. The expected outcomes include evidence to guide personalized rehabilitation approaches that combine cognitive and sensorimotor training.

### Strengths and Limitations

A key strength of this protocol is its multidimensional evaluation strategy, which combines subjective, performance-based, and digital assessment tools supported by literature. The inclusion of both healthy controls and myoelectric prosthesis users will allow for comparative analysis. However, this study is limited by its single-center design, specific prosthesis type (myoelectric only), and proprioception measurement restricted to predefined joint angles. In addition, sample size and recruitment feasibility may influence generalizability.

### Conclusions

Data collection and assessments are currently in progress, with data analysis planned after all participants have been assessed.

## Appendix

Multimedia Appendix 1 STROBE (Strengthening the Reporting of Observational Studies in Epidemiology) checklist for cross-sectional studies used in this study.

Multimedia Appendix 2 Peer-review report from the Tübitak 1002-A Rapid Support Module Review Committee, Scientific and Technological Research Council of Turkey.

## Abbreviations

BBT: Box and Block Test
BDI: Beck Depression Inventory
FRT: Functional Reach Test
JPS: joint position sense
JTHFT: Jebsen-Taylor Hand Function Test
MCT: Mental Chronometry Test
MI: motor imagery
MIA: motor imagery ability
MIQ-3: Movement Imagery Questionnaire-3
QuickDash: Disabilities of the Arm, Shoulder, and Hand
SMMSE: Standardized Mini-Mental State Examination
STROBE: Strengthening the Reporting of Observational Studies in Epidemiology
TÜBİTAK: Scientific and Technological Research Council of Turkey
VAS: visual analog scale
